### To minimize confounding interventions

 Prohibited treatments during the study. Probiotics, prebiotics, and foods containing probiotics (such as yogurt) other than those used in this study; Drugs for gastro-oesophageal reflux, such as acid inhibitors, antacids, gastric mucosal protectors, prokinetics, and equivalent drugs [19, 20] (see Additional file 1: Appendix 4) other than the study drug; Antibiotics and probiotics should be taken 2 h apart; Participants will be instructed to avoid spicy foods and to abstain from smoking or drinking during the study.

### Primary outcome

Based on faeces, the GM from day 0 (week 0), day 28 (week 4), day 56 (week 8), and day 84 (week 12) will be evaluated. For the GM assessment, DNA will be extracted from the stool samples with the QIAamp Fast DNA Stool Mini Kit (Qiagen, Hilden, Germany) following the manufacturer’s instructions, and the DNA quality will be examined by agarose gel electrophoresis and a Nanodrop spectrophotometer. Shotgun metagenomic sequencing will be performed on all samples by using an Illumina HiSeq 2500 instrument. Libraries will be constructed from DNA fragments ~ 300 bp in length and paired-end reads will be generated by sequencing 150-bp lengths in the forward and reverse directions. Meanwhile, the metagenomic analysis will include several components: the analysis of alpha and beta diversities in each group to understand whether the differences in the microbiota compositions of groups are significant, as well as the taxonomic characteristics of the study and control groups at the phylum, genus, and species levels to identify specific genes related to the individual differences in GERD. Metagenomic biological pathway analysis will be used to evaluate the effect of probiotics on the function of gut metagenomics in patients with GERD and, hopefully, to explore the metagenomic biological pathways contributing to the mechanism of probiotics in the treatment of GERD.

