**Method:**

This is a randomized, double-blind, placebo-controlled trial. A total of 120 eligible patients with GERD will be randomized into the experimental group or the control group. The treatment includes two phases: the initial treatment period lasts 8 weeks (weeks 1–8), and the maintenance treatment period lasts 4 weeks (weeks 9–12). During the initial treatment period, the experimental group will take rabeprazole and LiHuo probiotics, and the control group will take rabeprazole and a probiotic placebo; during the maintenance treatment period, the experimental group will take LiHuo probiotics, and the control group will take a probiotic placebo. The primary measure is the change in the GM. The secondary measures are the Reflux Disease Questionnaire (RDQ) score, Gastrointestinal Symptom Rating Scale (GSRS) score, faecal metabolome (FM), body mass index, Los Angeles grade of oesophagitis, adverse event (AE) rate and treatment compliance. Each outcome indicator will be assessed at day 0 (before administration), day 28 and/or 56 (during administration), and day 84 (end of administration) to reveal intragroup differences. AEs will be monitored to assess the safety of LiHuo probiotics.

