Moderate alterations to the upper and distal gut microbiota were observed in patients who used PPIs [8], and changes in the microbiota of the gastrointestinal tract are also associated with PPIs. Previous studies have shown that PPI use results in an increase in multiple taxa from the orders *Lactobacillales* (e.g., *Enterococcaceae* and *Streptococcaceae*) and *Bacillales* (e.g., *Staphylococcaceae*), as well as from the families *Pasteurellaceae* and *Enterobacteriaceae,* and a decrease in the families *Bifidobacteriaceae*, *Ruminococcaceae*, and *Lachnospiraceae* and the class *Mollicutes*. PPIs have the most significant impact on the microbiota in addition to antimicrobials according to the literature [9]. A study indicated that the GM of rheumatoid arthritis (RA) patients who were receiving PPIs was different, as *Streptococcus* was enriched in RA patients who received PPIs. The gut microbiota of PPI users could be modified by the production of virulence factors. This featured microbial function was positively correlated with the relative abundance of *Streptococcus* [10]. Frequent use of PPIs was associated with an increased risk of RA in women, with a higher risk observed in people with a longer PPI treatment period [11]. Researchers of one team observed positive effects of a multispecies probiotic in patients undergoing long-term PPI therapy. The richness of *Stomatobaculum* in the microbiome was decreased and that of *Bacillu*s increased during the intervention, and gastrointestinal quality of life simultaneously showed significant improvements. However, only sparse evidence can support the routine use of probiotics during PPI therapy [12].

In a clinical study on children, the incidence of gut microbial dysbiosis in children treated with PPIs combined with probiotics was only 6.2%, and 56.2% of children who used PPIs and placebo after 12 weeks developed gut microbial dysbiosis. Taking probiotics reduces the incidence of gut microbial dysbiosis in children receiving PPI treatment [13]. Additionally, probiotics can significantly reduce the frequency of reflux, promote gastric emptying, and improve reflux symptoms in infants [14, 15].

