### Intervention strength and management

Rabeprazole: 10 mg/tablet, from Eisai China, Inc (Tokyo, Japan).

LiHuo Probiotics powder: LiHuo probiotics powder containing strains such as *Lactobacillus casei Zhang*, *Bifidobacterium lactis* V9, and *Lactobacillus plantarum* P9, 2 g/bar, each bar containing active probiotics (≥ 50 billion CFU), were obtained from Jiangzhong Pharmaceutical Company Limited (China). During the manufacturing of LiHuo probiotics powder, *Lactobacillus casei Zhang*, *Bifidobacterium lactis* V9, and *Lactobacillus plantarum* P9 were mixed according to concentrations of ≥ 5 billion CFU/g, ≥ 15 billion CFU/g, and ≥ 5 billion CFU/g, respectively.

Probiotic placebo powder: The ingredients are maltodextrin, orange powder, and maltitol, and there are no active ingredients. The appearance, packaging, storage method, and dosing are the same as those of the LiHuo probiotics from Jiangzhong Pharmaceutical Company Limited (China).

The rabeprazole, LiHuo probiotics, and probiotic placebo will be stored in a cool, dry place away from light. Refrigerated storage will retain the maximum activity of the product. Each patient will receive a sample that corresponds to his or her unique number. All remaining study drugs and empty packages will be collected at the end of the study.

The study will have three phases: the screening period, the initial treatment period, and the maintenance treatment period. The interventions in each phase are described below:Screening: No intervention.Initial treatment (weeks 1–8):Control group: rabeprazole and probiotic placebo. The samples will be distributed to the patients every month.Experimental group: rabeprazole and probiotics. The samples will be distributed to the patients every month.Rabeprazole dosage: 10 mg/tablet twice a day before meals;Dosage of probiotic placebo or LiHuo probiotics: 2 bars, once a day, with or without water (< 40 °C), after meals. Thus, the daily dosage of probiotics is more than 100 billion CUF. Participants who take antibiotics should wait 2 h before taking the probiotic placebo or LiHuo probiotics.Maintenance treatment (weeks 9–12):

Control group: probiotic placebo. The samples will be distributed to the patients every month.

Experimental group: probiotics. The samples will be distributed to the patients every month.

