### Statistical analysis

First, the intention-to-treat (ITT) analysis will be conducted between the two groups, including all the intended participants who do or do not complete the follow-up. Then, per-protocol (PP) analysis will be conducted in the four-subgroup datasets according to compliance (100%, ≥ 80%, 60–80%, and < 60%) to validate the robustness of the results. The datasets will be analysed as described below.

With a randomized block design, the nonparametric rank sum test and Friedman M test will be performed to analyse the difference in each outcome measure at each time point (see “Intervention Outcome Measures” for details) between the two groups, including the GM analysis, RDQ score, GSRS score, faecal metabolomics, and BMI. The significance level will be set to *P* = 0.05. Next, the paired Wilcoxon signed-rank test will be performed for pairwise intragroup comparisons to analyse the change trends for each outcome measure before, during, and after the probiotic intervention. The significance level will be set at *P* = 0.05/[k(k-1)/2], where k is the number of groups in the comparison. For analysis of the oesophagitis grade, the diagnosis of LA-B at baseline and LA-A at week 12 indicates that the patient's oesophagitis grade will have decreased by one level. If the grade is LA-C at baseline and LA-A at 12 weeks, the patient’s oesophagitis grade will have decreased by 2 levels. The number of oesophagitis grades reduced by 1 and 2 levels in each group will be calculated. Then, a chi-square (*χ*^2^) test will be performed. AE rates in the two groups will be compared by the *χ*^2^ test or Fisher’s exact probability test based on the occurrence frequency of AE, and the difference in treatment compliance will be also examined by the *χ*^2^ test.

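### All post-baseline stool is sampled on product or at its last dose, and no step separates the product's own species, so beta-diversity, taxonomic and pathway differences can arise from ingestion alone

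*Protocol article*

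**What the plan says.** **Sampling.** Primary outcome states that "the GM from day 0 (week 0), day 28 (week 4), day 56 (week 8), and day 84 (week 12) will be evaluated". The Abstract (Method) labels these times "day 28 and/or 56 (during administration), and day 84 (end of administration"). It also says that "during the maintenance treatment period, the experimental group will take LiHuo probiotics, and the control group will take a probiotic placebo". Only rabeprazole stops at week 8. Table 1 has no visit after week 12, and its window of 2 days either side is not a washout.

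**Product.** Intervention strength and management states that "the daily dosage of probiotics is more than 100 billion" CFU and gives the minimum concentration of each strain.

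**Comparison.** Shotgun sequencing is applied to all stool samples. The arms are compared on alpha and beta diversity, "as well as the taxonomic characteristics of the study and control groups at the phylum, genus, and species levels", and on biological pathways. The article mentions no removal or separate reporting of the product's species.

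**Context.** Background says that PPI use raises several taxa "and a decrease in the families" that begins with Bifidobacteriaceae. The Abstract defines the primary measure broadly, as the change in the gut microbiome. Sample size names Chao1 at week 12 as the major indicator, with Shannon as a second index. Footnote 11 to Table 1 lets the faecal metabolome assay follow once the analysis finds a significant probiotic effect on the microbiome.

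**Time trend.** Statistical analysis sets out to "analyse the change trends for each outcome measure before, during, and after the probiotic intervention".

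**The concern.** Shotgun sequencing counts DNA from bacteria passing through the gut, live or dead, together with DNA from the resident community. Only one arm swallows the product, and every post-baseline sample is taken while it does or at the last dose. A between-arm difference can therefore mean that the resident flora changed, or only that patients took their sachets. The comparisons as described do not distinguish the two.

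Three things are at stake. First, because the primary outcome is the broad change in the microbiome, a beta-diversity or species-level difference caused by ingestion could be read as success. Second, the same difference could trigger the metabolome assay. Third, the planned comparison reaches to a time after the intervention, but no sample exists from that time, so persistence and colonisation cannot be shown.

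**Working it through.** **1. The plan's own figure.** Sample size gives, for Chao1, a difference of 145, SD 230, alpha 0.025 and power 80%. With n = 2 × [SD × (z_alpha + z_beta) / difference]² and alpha taken as two-sided:
- Chao1: 2 × [230 × (2.2414 + 0.8416) / 145]² = 47.83 (stated 47.9).
- Shannon: 2 × [0.8 × 3.0830 / 0.9]² = 15.02 (stated 15.0).

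Both reproduce. The checks below use 48 per arm, which is 60 less 20% dropout.

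**2. Dose.** (5 + 15 + 5) billion CFU/g × 2 g × 2 bars = 100 billion CFU/day. *B. lactis* supplies 15 × 4 = 60 billion, or 60%.

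**3. Product read share (assumption).** The documents give no figure. If daily faecal output T is 1e12 to 2e13 bacteria and all product DNA reaches the stool, the share is 1e11 / (T + 1e11): 9.1% at T = 1e12, 2.0% at 5e12 and 0.5% at 2e13. Incomplete recovery would lower it, so shares down to 0.01% (Shannon) or 0.1% (other measures) were also tried.

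**4. Chao1.** Three added species shift richness by about 3. The standardised shift is 3 / [230 × √(2/48)] = 3 / 46.95 = 0.064, which gives two-sided rejection of 5.05% at the 0.05 level. There is no material effect.

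**5. Shannon.** For product share f and resident index H, the mixed index is (1 − f)H + f·Hq + h(f). Here Hq = 0.950 for a 20:60:20 mix, and h(f) = −f ln f − (1 − f) ln(1 − f). Example with f = 1% and H = 3.5: 3.465 + 0.0095 + 0.0560 = 3.5305, a shift of +0.03. Over f = 0.01% to 10% and H = 2.5 to 4.5, the shift runs from −0.03 to +0.17 (natural log) and up to +0.36 (log base 2), against a planned 0.9. Rejection at 0.05 is 5% to 7% for f up to 1%. The worst case, f = 10% with H = 2.5, gives 18% (natural log) or 59% (base 2).

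**6. Beta diversity.** Simulation with the same resident flora in both arms: 150 species, 100,000 reads, product species absent natively, PERMANOVA at 0.05 with 199 permutations, 100 runs per setting. Rejection:

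| Product share | Bray-Curtis | Jaccard | Log-ratio |
|---|---|---|---|
| 0 | 4% | 0% | 4% |
| 0.1% | 6% | 100% | 100% |
| 0.5% | 14% | 100% | 100% |
| 2% | 61% | 100% | 100% |
| 5% | 100% | 100% | 100% |

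Two further simulations gave 75% (40 runs) and 73% for Bray-Curtis at 2%. With product species removed and abundances renormalised, Bray-Curtis rejection was 2% to 10%; a repeat gave 2.5% to 7.5%.

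**7. Taxa.** Rank-sum test, 1,000 runs per setting, residents unchanged. A product species otherwise absent from stool was significant in about 100% of runs at every share tried (0.1% to 5%). For genus *Bifidobacterium* (assumed log-SD 1.2 for residents and 0.7 for the product share), rejection was:

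| Resident median | Share 0.1% | 1% | 3% | 5% |
|---|---|---|---|---|
| 0.5% | 12.7% | 99.7% | 100% | 100% |
| 2% | 5.6% | 41.9% | 97.1% | 99.9% |
| 5% | 6.1% | 10.3% | 48.9% | 80.5% |

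Pathway comparisons use the same reads but were not quantified.

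**8. Before, during, after.** The intervention runs to week 12 and the last stool sample is at week 12. The samples cover before, during and the end of dosing; none covers a time after it.

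**The case against.** The strongest reply has four parts.

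- **The sized indicator is sound.** Chao1 barely moves, and Shannon moves little at low shares. This stands. A reader might infer that a microbiome effect is built into the trial's main result. The Sample size section does not support that, because the index that fixes the number of patients is essentially immune.
- **Silence is not inclusion.** The article names no profiler, distance or read filter, and a fuller plan could supply them. This stands in part: the claim is that no separation is stated, not that product reads are known to be kept. But the article itself fixes the sampling times, the compared quantities and the time-trend wording, and following them as written permits the misreading.
- **The magnitudes are assumed.** Read share, resident levels and distance metrics are not in the documents, and PERMANOVA is not named there. This stands. At a 0.5% share, 14% for Bray-Curtis (standard error about 3.5 points) is only modestly above the null rate. The Jaccard result is largely the presence or absence of added species, and its 0% null rate suggests that the simulated residents varied little in that respect.
- **Engrafted product strains may be part of the intended effect.** This is fair, and is why a filtered analysis should accompany the unfiltered one and not replace it.

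A reader might also expect a false recovery of *Bifidobacterium* and a false worsening of Lactobacillales. Neither is a planned endpoint. The first is an inference from Background. For the second, the examples given there are Enterococcaceae and Streptococcaceae, and no order-level comparison is planned.

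**Conclusion.** The point holds for beta diversity and taxa and, by the same mechanism but without a figure, for pathways. These comparisons can be significant with unchanged resident flora. Product-species tests and presence/absence or log-ratio distances are exposed even at a 0.1% share, provided the product species are otherwise absent. Bray-Curtis and genus *Bifidobacterium* are exposed mainly from about 1% to 2% upward; the genus result also depends on resident levels.

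It does not hold for Chao1, and matters little for Shannon unless the share is high and resident diversity low. All percentages rest on assumed read shares and community structures, so they show what is possible and do not forecast this trial.

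Separately, and without any modelling, the time-trend wording promises a period that has no sample. The Abstract's label for day 84 suggests that the end of dosing was meant, so this is a wording error. It would become a substantive one if day 84 were used to claim persistence.

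**What to change.** - **Primary outcome:** state that between-arm beta-diversity, taxonomic and pathway comparisons will also be reported with reads of *L. casei*, *B. lactis* and *L. plantarum* removed and abundances renormalised, in both arms and at all visits. State that any claim of change in the resident microbiome must hold in this filtered analysis, and report product-species abundance separately as an exposure marker.
- **Table 1, footnote 11:** require the microbiome effect that triggers the metabolome assay to hold in the filtered analysis.
- **Statistical analysis:** change the time-trend wording to before, during and at the end of the intervention, and make no persistence or colonisation claim from day 84. Such a claim would need a sample taken after dosing has stopped.

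The cost is one bioinformatic filter and one extra set of tables. No new sample, visit or patient is needed. The drawback is that some native reads of the same species are also removed, which is acceptable because the unfiltered results are reported alongside.

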### Secondary outcome

RDQ score: The RDQ (see Additional file 1: Appendix 5) includes 4 symptoms: heartburn, acid reflux, regurgitation, and noncardiac chest pain. Each symptom is rated on a 0–5 scale based on its frequency and severity in the last week. The total score is 40, and a higher score is associated with more severe symptoms. RDQ ≥ 12 indicates GERD [18, 21]. The RDQ will be used to evaluate reflux-related symptom scores on day 0 (week 0), day 28 (week 4), day 56 (week 8), and day 84 (week 12).GSRS score: The GSRS (see Additional file 1: Appendix 6) is a self-rating scale that includes 15 items in 5 subscales (abdominal pain, acid reflux, dyspepsia, constipation, and diarrhoea). Each item is rated on a Likert scale ranging from 0–3 (none, mild, moderate, mild) based on the severity of symptoms in the last week. The total score is 45, and a higher score is associated with more severe symptoms [22–24]. The GSRS will be used to evaluate gastrointestinal disease symptom scores on day 0 (week 0), day 28 (week 4), day 56 (week 8), and day 84 (week 12).Faecal metabolome (FM): Based on the faeces, FM from day 0 (week 0), day 28 (week 4), day 56 (week 8), and day 84 (week 12) will be evaluated. Stool samples will be extracted using the protein precipitation method, and the supernatant will be transferred to sample vials for mass spectrometry combined with liquid chromatography (LC–MS/MS) analysis. The original data will be subjected to peak alignment, retention time correction, and peak area extraction through the XCMS-Plus program. The structure of metabolites will be identified by accurate mass matching (< 5 ppm) and two-level spectrum matching, and the METLIN database will be retrieved. Missing values > 50% in the group will be deleted, and the data will be normalized. Multidimensional statistical analysis will then be carried out, including unsupervised principal component analysis (PCA), supervised partial least squares discriminant analysis (PLS-DA) and potential differential metabolite analysis. Metabonomic analysis could further identify the potential differential metabolites of probiotics in the treatment of GERD, and correlation analysis between the gut microbiota and metabolites could be performed.Change in the Los Angeles (LA) grade of oesophagitis: According to gastroscopy, the change in the LA grade of oesophagitis will be evaluated.Body mass index (BMI): BMI = weight (kg)/height (m)^2^. BMI will be measured in the morning using the same weight and height scales at each visit. Participants will be instructed to wear light clothing and take off their shoes (standing barefoot or wearing socks no thicker than 0.1 cm) during the weight and height measurements.AE rate: all the AEs collected as described below will be used to calculate the AE rate in each group.Treatment compliance will be monitored as described in the “Volunteer compliance monitoring” section. Although efforts have been made to promote treatment compliance, there may still be differences between the two groups due to AEs.

### Safety evaluation

AEs will be evaluated with blood tests, urine analysis, and stool tests (> 2 × ULN or < 2 × LLN); liver tests (ALT, AST, total bilirubin); renal tests (Scr, blood urea nitrogen); and ECG. AEs may be related or unrelated to the study interventions.At each visit, the patients will be asked about any AEs with nondirective questions. Patients may also voluntarily report AEs.Severe adverse events (SAEs) are events that occur after the study interventions are provided and result in hospitalization, prolonged hospitalization, disability, impaired ability to work, threats to the patient’s life, or death. All SAEs must be reported to the Ethics Committee of the hospital and the sponsor. Participants with SAEs will discontinue the interventions.Treatment-related AEs must meet the following criteria: a reasonable temporal/causal relationship with the treatment; side effects unrelated to comorbidities or concomitant medications; improvement or resolution of AE symptoms after treatment discontinuation; and causality can be explained with a pharmacological, biological, or phenomenological mechanism.

Drug-related AEs: possible adverse reactions experienced while taking rabeprazole include allergies (rash, itching, urticaria), abnormal blood test results, abnormal biochemical parameters, high blood pressure, gastrointestinal symptoms (constipation, diarrhoea, abdominal distension, nausea, lower abdominal pain, bitter taste in the mouth), headache, dizziness, palpitations, fever, fatigue, hypoesthesia, dry mouth, blurred vision, and vomiting. Possible serious adverse reactions include shock, interstitial nephritis, liver dysfunction, jaundice, anaemia, and hyponatremia. Possible adverse reactions to probiotic ingestion include diarrhoea, constipation, and weight loss.

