### Volunteer recruitment

Posters will be disseminated at the hospital to recruit participants. During their appointment at the Department of Gastroenterology in the First Affiliated Hospital of Nanchang University, volunteers who are interested in the study will undergo preliminary evaluations based on the inclusion and exclusion criteria. Additionally, the investigator will explain the purpose, process, and potential benefits and risks of this study, and the volunteers may choose to participate by signing the informed consent form. Next, the volunteers will undergo further screening to determine their eligibility. Eligible participants will receive the study intervention and follow-up. The following steps describe the formal intervention and follow-ups (Table 1).

**Table 1 Tab1:** Study and follow-up schedule

Item^1,10^		Screening	Baseline	Initial treatment		Maintenance treatment
		Visit 0	Visit 1	Visit 2	Visit 3	Visit 4
		Days −3 to 0	Day 0	Week 4	Week 8	Week 12
Basic demographics		X				
Vital signs, physical examination		X				
Allergies, medical history^2^, medication history^3^, surgical history^4^		X				
Smoking and drinking		X				
Gastroscopy		X^5^				X^6^
Abdominal ultrasound B^7^		X				
Serum human chorionic gonadotropin (hCG)		X				
ECG		X				X
Blood test, urine analysis, stool test (including occult blood)		X				X
Liver/kidney function^8^		X				X
Signed informed consent		X				
Inclusion/exclusion criteria verification			X			
Primary outcome measure	GM^11^ (metagenomics)	X		X	X	X
Secondary outcome measures	RDQ	X	X	X	X	X
	GSRS		X	X	X	X
	Faecal metabolomics^11^	X		X	X	X
	BMI ^9^		X	X	X	X
	LA grade	X				X
Safety measures	AEs			X	X	X
	SAEs			X	X	X
Compliance verification			X	X	X	
Concomitant medications		X	X	X	X	

^1^Visit window: 0 days for visit 1; ± 2 days for visits 2, 3, and 4

^2^Medical history: current and past illnesses, including peptic ulcer, gastritis, oesophagitis, cardiovascular and cerebrovascular diseases, cancer, and mental illness

^3^Medication history: PPI, histamine H2 antagonists, antibiotics, probiotics, prokinetics, gastric mucosal protectors, and other drugs for gastro-oesophageal reflux (including herbs)

^4^Surgical history: gastrointestinal surgeries, including gastro-oesophageal and duodenal surgeries

^5^Performance of gastroscopy in domestic tertiary or higher hospitals in the past 3 months

^6^Gastroscopy at visit 4, LA grades at visit 0 and visit 4 referring to patients with oesophagitis (LA-A, LA-B or LA-C)

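### The low laboratory limit for adverse events is set at twice the lower limit of normal, so normal results meet the adverse-event criterion that feeds a secondary outcome

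*Protocol article*

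**What the plan says.** The Safety evaluation section of the protocol article states that "AEs will be evaluated with blood tests, urine analysis, and stool tests", and the bracket closing that list gives the limits: "stool tests (> 2 × ULN or < 2 × LLN". Liver tests, renal tests and ECG follow after the bracket and have no limit of their own there. The section adds that "AEs may be related or unrelated to the study interventions".

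The AE rate is one of the secondary measures named in the abstract: "Los Angeles grade of oesophagitis, adverse event (AE) rate and treatment compliance". The Secondary outcome section builds it from the Safety evaluation section: "all the AEs collected as described below will be used to calculate the AE rate in each group". The Statistical analysis section then tests it: "AE rates in the two groups will be compared by the" chi-square or Fisher's exact test.

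Table 1 (under Volunteer recruitment) schedules the row "Blood test, urine analysis, stool test (including occult blood") at screening and at visit 4, week 12. Each participant therefore has one post-baseline set of these tests.

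**The concern.** The two sides of the limit look symmetrical but are not. Doubling the upper limit moves the cut away from the reference range. Doubling the lower limit moves the cut into the range, or past its top. A participant with an entirely normal result can therefore meet the printed criterion for a laboratory AE.

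The rule reaches a tested outcome. The AE rate takes in every AE collected under this section and has no relatedness filter, so nothing downstream removes the false events. Because they arise in both arms alike, the main harm is dilution: a true difference in AE rate between probiotic and placebo would be buried under events that are not events.

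**Working it through.** The article states no expected AE rate, so there is no figure to reproduce. The check is on the rule itself.

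**Step 1. The rule, with no assumptions.** For LLN > 0, 2 × LLN > LLN. Every value from LLN up to 2 × LLN (or up to ULN, if that is lower) is in range and also flagged. If ULN < 2 × LLN, the whole reference range is flagged. For example, an assumed range of 120–160 gives a cut at 2 × 120 = 240, above 160, so every normal value is flagged. An assumed range of 125–350 gives a cut at 250, and (250 − 125)/(350 − 125) = 56% of the width of the range is flagged.

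**Step 2. Share of healthy values flagged per analyte.** The article gives no reference ranges, so I varied R = ULN/LLN (assumption). I took the reference range as the central 95% of healthy values and set LLN = 1, ULN = R.

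- Normal model: mean (1 + R)/2, SD (R − 1)/3.92, share = Φ((2 − mean)/SD).
- Log-normal model: log mean ln(R)/2, log SD ln(R)/3.92, share = Φ((ln 2 − log mean)/log SD).

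| R | Normal | Log-normal |
|---|---|---|
| 1.5 | 100% | 100% |
| 2 | 97.5% | 97.5% |
| 2.5 | 74% | 84% |
| 3 | 50% | 70% |
| 4 | 26% | 50% |
| 8 | 8% | 26% |

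For comparison only, a cut exactly at the LLN would flag 2.5% by construction.

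**Step 3. At least one flag per participant.** One analyte with R ≤ 2 flags nearly every tested participant. With ten independent analytes under the normal model, R = 3 gives 1 − 0.5^10 = 99.9%, and R = 4 gives 1 − (1 − 0.257)^10 = 95%.

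**Step 4. Effect on the comparison.** Inputs: 60 per arm (Sample size section); 80–95% of participants tested at week 12, where 80% corresponds to the 20% loss allowed for in that section and 95% is assumed; all tested participants flagged (assumption, supported by steps 2 and 3); true AE rates of 10% versus 30% (assumption).

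Observed rate = 1 − (1 − true rate) × (1 − share tested).

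- 80% tested: 1 − 0.90 × 0.20 = 82%, and 1 − 0.70 × 0.20 = 86%.
- 95% tested: 1 − 0.90 × 0.05 = 95.5%, and 1 − 0.70 × 0.05 = 96.5%.

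Power, two-sided 0.05: Φ{[d − 1.96 √(2 p̄(1 − p̄)/n)] / √[(p₁(1 − p₁) + p₂(1 − p₂))/n]}, where d is the difference in rates and p̄ their mean.

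- Correct rule, 10% versus 30%: (0.20 − 1.96 × 0.0730)/0.0707 = 0.80, power 79%.
- 82% versus 86%: (0.04 − 1.96 × 0.0669)/0.0668 = −1.36, power 8.6%.
- 95.5% versus 96.5%: (0.01 − 1.96 × 0.0358)/0.0358 = −1.68, power 4.6%.

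With true rates of 20% versus 40%, power falls from 67% to between 4.8% and 9.2%.

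**The case against.** The best defence is that nobody would apply the limit as printed. The section says that AEs are evaluated with these tests, not that every value past the limit is automatically an AE. Its list of possible rabeprazole reactions speaks of abnormal blood and biochemical results, so abnormality is clearly what was meant. This stands as far as it goes: the limit is probably a slip and the trial may never suffer the dilution. It does not rescue the text. If staff follow the rule, the comparison is uninformative. If they ignore it, the definition in use is not the published one.

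The scope is also limited. I read the bracket as covering the blood, urine and stool tests; it does not extend to the liver, renal and ECG items. It has no effect where the LLN is zero or the result is qualitative, as can happen in urine and stool testing. The primary outcome and sample size are untouched, and the AE rate is one of seven secondary measures.

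Two stronger readings are tempting. A reader might infer that all 60 participants in each arm would have an AE. That is an upper bound: the tests have one post-baseline occasion, up to 20% loss is allowed for, and the reference ranges are not given.

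A reader might also infer that the relatedness rule, which requires "improvement or resolution of AE symptoms after treatment discontinuation", distorts the same outcome. It does not, because the AE rate uses all AEs and no related-only test is stated. Nor does the rule exclude everyone who continues treatment: rabeprazole stops for all after week 8 while the powder goes on to week 12, and participants with SAEs discontinue the interventions. Whether only values new or worse than at screening should count is a convention that an article commonly leaves to the full protocol or analysis plan.

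**Conclusion.** The low limit is wrong as written. That rests on the text alone: for any quantitative analyte in the covered tests with an LLN above zero, in-range values meet the AE criterion, and nothing else in the article corrects this.

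The size is conditional. It assumes literal use, at least one analyte with ULN no more than about twice the LLN (or several with a ratio of roughly 2.5 to 4), and illustrative true AE rates. Under those assumptions most tested participants in both arms would carry an AE, and the power of the AE comparison would drop to about the nominal significance level or little above it. The documents do not support saying that the AE rate will in fact saturate or that the published rate will be meaningless. The error should be corrected because it defines a tested outcome and the correction is trivial.

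**What to change.** In the Safety evaluation section, restate the low laboratory limit so that no value within the reference range counts as a laboratory AE. The sponsor's safety team should set the actual limit; none is proposed here. State which tests the limit covers, and apply the corrected definition when the AE rate is calculated and compared under the Secondary outcome and Statistical analysis sections.

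The cost is a one-line protocol correction and matching programming of the laboratory AE flag. No new tests, visits or participants are needed. If laboratory AEs have already been recorded under the printed limit, they can be re-derived from the stored results, ideally before unblinding.
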